#### Maternal secondary outcome measures

The *Clinical Global Impressions – Severity Scale (CGI-S)* [81] is a clinician-rated evaluation of symptom severity ranging from 1 (normal, not ill) to 7 (very severely ill). The CGI-S is commonly used in clinical trials and in a routine clinical setting, has shown to be sensitive to clinical change in diagnostically diverse populations including those diagnosed with depression and anxiety [83]. The CGI-S will be administered by graduate students under the supervision of a clinical psychologist and will assess the severity of mood, anxiety and global functioning.

*The Montgomery and Asberg Depression Rating Scale (MADRS)* [84] is a 10 item clinician-rated scale that assesses the frequency, severity and duration of depressive symptoms over the previous week. Each item is rated on a 7-point scale ranging from 0 to 5, with a maximum score of 60. A greater score indicates more severe symptoms. The MADRS demonstrates excellent reliability and good validity [84].The MADRS will be administered by psychology graduate students using the Structured Interview Guide for the Montgomery-Asberg Depression Rating Scale (SIGMA) [85] under the supervision of a clinical psychologist. The SIGMA has demonstrated good to excellent interrater reliability and intraclass correlation (r = 0.93) [85].

*Depression Anxiety Stress Scale 21 (DASS21)* [86] is a 21 item self-report questionnaire with three, seven item subscales measuring the severity of depression, anxiety and stress, each summing to a maximum score of 21 with elevated scores indicating more severe symptoms. Each item on the DASS-21 is rated on a four point scale ranging from 0 (did not apply to me at all) to 3 (applied to me very much, or most of the time). The DASS-21 provides clinical cut-off scores for each subscale ranging from normal to extremely severe. The DASS-21 has been widely used in both clinical and non-clinical populations and has demonstrated strong validity and internal consistency (α = 0.95 depression, 0.90 anxiety, 0.93 stress, 0.97 total score) [87].

*Generalized Anxiety Disorder – 7 item (GAD-7)* [88] *is* a 7-item self-report measure of generalised anxiety symptoms over the past 2 weeks. Each item is rated on a 4-point scale ranging from 0 (not at all) to 3 (nearly every day). Total scores range from 0 to 21 with higher scores indicating more severe symptoms. The GAD-7 includes the following cut off scores: normal: 0–4; mild: 5–9; moderate: 10–14 and severe: 15–21. The GAD-7 has demonstrated good internal consistency and test-retest-reliability for diagnosing generalised anxiety disorder in the general population [88, 89]. In perinatal populations, the GAD-7 has yielded a sensitivity of 61.3% and specificity of 72.7% at a cut off score of 13 [90].

*Perceived Stress Scale (PSS)* [91] is a 10 item self-report questionnaire measuring an individual’s experience of stress on a 5-point scale ranging from 0 (never) to 4 (very often). Total scores range from 0 to 40 with higher scores indicating greater levels of stress. The PSS includes cut off scores to indicate the severity of stress: low: 0–13; moderate: 14–26; high: 27–40. The PSS has established test-retest reliability and internal consistency (α= > 0.70) in culturally diverse populations including pregnancy [92].

*Short Form Health Survey – 12 version 1 (SF-12v1)* [93] a 12 item self-report questionnaire assessing physical and mental components of health related quality of life over the previous 4 week period. Total scores from each component ranges from 0 to 100 with higher scores indicating better quality of life. The SF-12 has demonstrated good reliability and validity in the general population [93] and for a variety of severe mental health diagnoses [94]. The SF-12 has demonstrated excellent internal consistency in both the first (α = 0.83) [95] and third (α = 0.84) trimester of pregnancy [96].

*Difficulties in Emotion Regulation Scale – Short Form (DERS-SF)* [97] is an 18 item self-report questionnaire assessing emotion dysregulation across six subscales which identify lack of awareness, clarity, acceptance, access to strategies, engagement in goal-directed activities and ability to manage impulses when experiencing negative emotions. Cronbach’s alpha coefficient for each subscale ranged from 0.75 to 0.92 in an adult population [98].

*Global Assessment of Functioning (GAF)* [99] is a clinician-rated scale included in the DSM-III-R, that considers the severity of social, psychological and occupational functioning of mental health not due to physical or environmental limitations. The GAF is measured on a scale of 0–100, a higher score indicating a higher level of functioning and includes the following cut-off scores: normal: 91–100; mild: 61–90; moderate: 31–60; severe: 0–30. The GAF has demonstrated excellent reliability (ICC = 0.92) [100].

*The Antidepressant Side-Effect Checklist (ASEC)* [101] is a list of 21 symptoms that assesses side effects of the intervention. The ASEC asks participants to indicate the severity of their symptoms on a four-point scale ranging from 0 (absent) to 3 (severe). The ASEC is a self-report assessment of side effects and has been adapted to include further symptoms including rash, itching and numbness, pain, burning or tingling in hands, feet or legs associated with vitamin toxicity. The ASEC is well used and validated in antidepressant drug trials and has been adapted for use with multinutrients. Interrater reliability of each item on the ASEC ranges from 0.55 to 0.89 and internal consistency was adequate ranging from 0.77 to 0.78 [101].

*The Pittsburgh Sleep Quality Index (PSQI)* [102]*)* is a 19 item self-report questionnaire that assesses sleep quality, sleep latency, sleep duration and disturbance, habitual sleep efficiency, sleep medication usage and daytime dysfunction over the past month. Each item is rated on a four point scale ranging from 0 to 3 with “poor” sleep indicated at a sum score of five or more [102]. In pregnancy cohorts, the PSQI has demonstrated good construct validity [103] and internal consistency (α = 0.69–0.81) [103–105].

*Treatment Satisfaction Questionnaire for Medication – 11 (TSQM-11)* [106] *is* an 11 item self-report questionnaire assessing how satisfied participants are with using the multinutrients and the effect of the multinutrients on three domains: effectiveness, convenience and global satisfaction. Each item is rated on a seven point scale ranging from extremely dissatisfied to extremely satisfied with total scores ranging from 0 to 100; higher scores indicating greater satisfaction. The TSQM-11 has demonstrated internal consistency (α = 0.84–0.94) and high test-retest reliability (ICC= > 0.7) [106].

*Biomarkers* of inflammation (interleukin- 4, interleukin- 6, interleukin- 10 and tumor necrosis factor-α) and nutrients (vitamin B12, vitamin D, zinc, copper, ferritin, iron, homocysteine, ceruloplasmin, folate) will be analysed from blood samples. A haematology blood count will also be performed.

#### Maternal covariate outcome measures

Additional outcomes will be used to assess any mediating or moderating impacts on the treatment outcome.

The *Multidimensional Scale of Perceived Social Support (MSPSS)* [107] is a 12 item self-report scale measuring the subjective adequacy of social support from family, friends and significant others over the previous 8 week period. Items on the MSPSS are rated on a seven-point scale ranging from one to seven with higher scores indicative of greater social support. The MSPSS has demonstrated good internal and test-retest reliability and moderate construct validity [107]. In the pregnant population, the MSPSS has shown excellent internal consistency (α = 0.90–0.92) [104, 108].

*Stressful Life Events Questionnaire (SLEQ)* [109] is a 26 item self-report questionnaire assessing the incidence of stressful life events. The scale will be modified for the purposes of this study to exclude the item “you suffered from a mental illness” and include the following items: “You moved house”, “You got married”, “You had a pet go missing, die or have you had to rehome it”. The SLEC was developed for and originally used in a study examining the impact of maternal stress during pregnancy on cognitive development and fearfulness in infancy [109].

*Heaviness of Smoking Index (HIS)* [110] is a two item self-report questionnaire assessing a person’s level of nicotine dependence with higher scores indicating a more severe dependence. For the purposes of using an online assessment tool, the question “Over the past two weeks, have you smoked a cigarette?” will be added to identify whether or not participants have used cigarettes. The HIS has shown to good reliability (r = 0.72–0.70) and predictive validity, whereby higher scores have been associated with subsequent quit attempts [111].

*The AUDIT - Consumption (AUDIT-C)* [112] is a 3 item self-report questionnaire to assess alcohol consumption and identify hazardous drinkers or active alcohol use problems. Items are rated on five-point scale (0–4) with total scores ranging from 0 to 12; higher scores indicating alcohol consumption as a greater risk to safety. A score of three or more has demonstrated the optimal sensitivity (0.66) and specificity (0.94) for identifying alcohol dependency or abuse [112]. In pregnancy populations, the AUDIT-C has shown to be the most sensitive tool for identifying alcohol dependency or abuse (0.71) with excellent sensitivity (0.98) and high specificity (0.85) [113].

*Drug Abuse Screening Test - 10 (DAST-10)* [114] *is* a 10 item self-report questionnaire assessing drug use and dependence and has been adapted for the purposes of this study. Participants who identify to have used drugs over each two-week period will be asked questions 1, 3 and 9 of the DAST-10, which have demonstrated a Cronbach’s alpha of 0.55, 0.69 and 0.78 respectively. Participants will also be asked to identify what substances they have used.

*Dietary Screening Tool (DST)* [115] is a 24 item self-report questionnaire that assesses dietary intake and identifies those at nutritional risk. The DST has a total score of 100 with higher scores indicating a healthier dietary pattern. The DST has yielded good sensitivity (0.83) and specificity (0.75). The DST has been adapted to include New Zealand foods for the purposes of this study.

*Dietary Inflammatory Index (DII)* [116] lists 45 foods and nutrients that positively or negatively affect levels of inflammation. Data from a three-day food diary developed for the purposes of this study will be used to calculate a DII with higher scores indicating greater anti-inflammatory effects of foods.

*The Helping Alliance Questionnaire (HAQ)* is a five item self-report questionnaire developed for the purposes of the study to assess the extent to which the participant has an alliance with the assessor. Each item is rated on a 6 point scale from 0 (strongly disagree) to 5 (strongly agree) with higher scores indicating a greater alliance.

*The Dutch Measure for quantification of Treatment Resistance in Depression (DM-TRD)* [117] is a refined and extended staging measure of the Maudsley Staging Method [118] used to predict treatment resistance, severity of future depressive symptoms and remission. The DM-TRD will be scored based on outcomes from the SCID-5RV, GAF, Standardised Assessment of Personality – Abbreviated Scale (SAPAS) [119] and questions developed for this study to assess past treatment and therapy.

*Anthropometry.* Participants height, weight and blood pressure (systolic, diastolic and pulse) will be taken throughout the trial.

#### Infant measures

The *Brazelton Neonatal Behavioural Assessment Scale (NBAS)* [120] is a comprehensive assessment of both neurological integrity and behavioural functioning. The NBAS will be administered by a graduate student to assess the full range of infant neurobehavioral performance (orientation to auditory and visual stimuli) including infant stress (colour changes, tremors, startles), self-soothing capabilities, states and their organisation within the first 2 weeks after birth. The NBAS is a highly utilized measure in infant studies and has been found to have good internal consistency (Cronbach’s α = 0.94) and test-retest reliability [121]. The assessment will be separated into seven clusters for scoring purposes, with each of the NBAS items given a score (ranging from 1 to 9). Higher scores typically indicate better performance, with a lower score typically indicating poorer performance. There are some items however, in which the opposite is the case or where a midpoint score is more optimal. Each participant will be scored on each individual item using the aforementioned scales, and given a total in each of the seven clusters.

The *Still-Face Experiment (SFE)* [122] is a video-taped observational task used to assess mother-infant interaction. The SFE has been used in a wide range of development studies to assess infant affect, emotional regulation and maternal sensitivity within infant-mother dyads [123–126]. The still-face video footage will be coded on a second-by-second basis using the Infant and Caregiver Gaze by Affect/Engagement Phases (ICEP). Behaviours exhibited by mother and baby will be coded into one of nine categories. The nine ICEP categories will be collapsed into the following three categories, both for maternal and child behaviours: negative (negative engagement, hostile/intrusive, withdrawn), neutral (non-infant focused engagement), and positive (social monitor/no vocalizations or neutral vocalizations, social monitor/positive vocalizations, social positive engagement, exaggerated positive engagement). To measure dyadic matching behaviours, the proportion of time in which each mother and infant present with matched/mismatched behaviours during both the play and reunion phases will be calculated.

The *Postpartum Bonding Questionnaire (PBQ)* [127] is a 25-item self-report questionnaire that assesses maternal attitudes and feelings towards her infant. The questionnaire consists of four subscales that reflect impaired bonding, rejection and anger, anxiety about care and risk of abuse. Each of the subscales utilises a six-point scale, ranging from “always” to “never”. Responses to positive questions, such as “I enjoy playing with my baby”, will be scored from 0 (“always”) to 5 (“never”). Responses to negative questions, such as “I am afraid of my baby”, will be reverse scored from 5 (“always”) to 0 (“never”). The scores are summated, with a higher score in each of the four subscales indicating problematic bonding. The PBQ has been demonstrated to have acceptable internal consistency (Cronbach’s α = 0.76) [128].

*Infant Behaviour Questionnaire (Revised) (IBQ-R)* [129] is being used to assess infant temperament through a 36-item self-report questionnaire. Questions will be separated into six subscales to measure different temperament dimensions (smiling and laughter, distress to limitation, soothability, activity level, fear, and duration of orientation). They are answered on an eight-point scale with responses ranging from [1] never to [7] always. There is also a “does not apply” option if the event in question had not occurred at the time point of interest. Responses for each individual subscale are summed, with higher scores indicating greater levels of that temperament dimension. Each of the six subscales of the IBQ has been reported to have acceptable or good internal reliability; smiling and laughter (α = 0.85), distress to limitation (α = 0.84), soothability (α = 0.84), activity level (α = 0.73), fear (α = 0.80) and duration of orienting (α = 0.72) [129].

*Crying Patterns Questionnaire (CPQ)* [130] assesses infant crying patterns and feeding methods over 7 consecutive days and has been widely used in studies assessing crying in infants up to 9 months [130–132]. The questionnaire contains ten questions, providing information on length and frequency of crying episodes and soothing techniques for a typical day within the last week. Length and frequency of crying will be collected in hours or minutes to give a proportion of time spent crying during the day, with higher proportions indicating higher incidence of unsoothability. Frequency of soothing techniques will be scored on a four-point scale, from “never used” to “used repeatedly each day”. When compared to data collected using a diary, moderate to good convergence between maternal reports in the CPQ and diaries was found [133].

*Ages and Stages Questionnaire: Social-Emotional (ASQ-SE)* [134]*)* is a 22-item self-report questionnaire used to assess infants self-regulation, compliance, communication, autonomy, affect and interaction with people. Each question is scored on a three-point scale indicating whether the infant displays the behaviour in question [1] most of the time, [2] sometimes, or [3] never or rarely, and whether or not that particular behaviour is a concern to the parents. Each response will be given a score of 0–10, with an additional 5 points added if the parents identify a concern, and then summed. Scores can be interpreted as either above or below cut-off score (2 month = 35; 4/6 month = 45) with higher scores indicating problems with behavioural development. The ASQ has been found to have good test-retest reliability, measured as a percentage of agreement between questionnaires, found to be 94% [134]. Concurrent validity using standardized measures yielded an overall agreement of 85%, with a range of 76–91%. Internal consistency in each of the domains has been found to range between 0.49 to 0.63 when assessed at 4 months [134].

Infant sleep development will be assessed using a 24 h sleep diary adapted from Henderson [135] that will be completed by a caregiver over 2 consecutive days, once per month.

*Birth outcomes and infant anthropometry* will be assessed via participant’s medical records and will include gestational age, weight, height, head circumference, Apgar score, mode of birth, length of labour, medications during labour/birth and the postnatal period, cord clamping, type of feeding, and vitamin K injections.

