### Aims

This trial aims to investigate the efficacy and safety of a broad-spectrum multinutrient formula compared to an active control formula for the treatment of symptoms of antenatal depression and anxiety using a double blind randomized controlled design. We anticipate that women randomized to receive the multinutrient formula will show a greater improvement in depressive and anxiety symptoms compared to women taking the active control formula. We hypothesise that improvements will generalise to secondary measures of sleep, stress, emotion regulation and quality of life.

An exploratory aspect of this trial aims to document potential effects of an enriched nutrient environment during utero on infant outcomes. As such, we will explore whether length of exposure to nutrients is a predictor of infant temperamental outcomes. We hypothesise that a more nutrient-rich foetal environment will contribute to more positive long-term health and developmental outcomes for the infant.

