All data will be analysed on an intention-to-treat basis using the last observation carried forward method and as such will include all participants’ data regardless of treatment compliance. Treatment adherence will be measured by the total number of capsules consumed throughout the trial phases. Only participants who consume 70% or more of the total number of capsules will be considered adherent to the treatment. A per-protocol analysis, which excludes participants with protocol violations (e.g. drop out, non-adherence to treatment consumption) will be performed on the primary outcomes (EPDS and CGI-I) in order to compare differences in treatments responses between participants who were adherent with the treatment and those who discontinued participation or were non-adherent. Outcomes from the open label phase will be compared to the group outcomes from the week 12 observation of the RCT phase using generalised linear mixed effects regression models taking into account participants self-reported use of micronutrients.

To assess the effect of the multinutrient intervention has on infant development, we will compare those infants exposed to the multinutrients versus those infants not exposed to the multinutrients on emotional, cognitive and physical development. Length of exposure to the multinutrients (due to the RCT phase and varying starting points during gestation) and score on the EPDS will also be considered as continuous variables in considering infant outcomes. Hierarchical regression analysis will be run using Stata 15 in order to identify if perinatal/postpartum depression and multinutrient exposure are predictors of improved self-regulation of the infant across the various time points. Descriptive statistics for each participant will be used to compare demographic characteristics between the treatment groups to allow any differences to be controlled.

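### IBQ-R temperament subscales are plain sums although items can be marked not applicable, so scores are not comparable between infants or time points

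*Protocol article*

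**What the plan says.** The scoring is described in the Protocol article, Infant measures, in the paragraph on the IBQ-R.

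- The instrument "is being used to assess infant temperament through a 36-item self-report questionnaire".
- On its structure, the article says: "Questions will be separated into six subscales to measure different temperament dimensions". The number of items in each subscale is not given.
- On the ratings, it says: "They are answered on an eight-point scale with responses ranging from [1] never to [7] always".
- A further answer stands outside those ratings: an "option if the event in question had not occurred at the time point of interest", meaning that the item does not apply.
- The scoring rule follows directly: "Responses for each individual subscale are summed, with higher scores indicating greater levels of that temperament dimension".

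The article gives the not-applicable answer no numerical value. It does not mention averaging over answered items, proration or a minimum number of answered items.

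Temperament matters to the trial because the Aims say that "we will explore whether length of exposure to nutrients is a predictor of infant temperamental outcomes". This stands within what the Aims call an exploratory aspect. The Data analysis section plans to compare exposed with unexposed infants, to use length of exposure as a continuous variable, and to run hierarchical regressions for self-regulation at several time points. Its general rule on missing data is that "All data will be analysed on an intention-to-treat basis using the last observation carried forward method".

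**The concern.** A summed subscale score has a stable meaning only if every infant is scored on the same items. Here the questionnaire itself allows the set of scored items to vary, since the not-applicable answer is tied to whether an event has yet occurred. Two infants with the same ratings on every item that applies to them can therefore receive different sums. The stated interpretation, that a higher score means more of the dimension, then no longer follows from the stated rule.

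Applicability may also change as an infant gets older. In that case a change in the sum between time points could partly reflect a change in the number of scored items, with no change in temperament. What is at stake is how the infant temperament results can be read; no maternal result depends on it.

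**Working it through.** The article states no figure that depends on this rule, so there is nothing to reproduce. The check is direct arithmetic on the rule.

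**Inputs**

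- Items: 36. Subscales: 6. Rating range: 1 to 7. All from Infant measures.
- Items per subscale, k: not stated. Equal length would give 36/6 = 6. This is an assumption, so k = 4 and k = 8 are shown as well.
- Number of not-applicable items, m: not stated; shown for 0 to 3.
- Rating r, held constant over the applicable items so that temperament is the same in every row.

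**Case A: the not-applicable answer adds nothing.** The sum is r(k − m). Relative to the full sum rk, the shortfall is m/k, whatever r is. With k = 6 and r = 5:

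| m | Sum | Change |
|---|---|---|
| 0 | 5 × 6 = 30 | none |
| 1 | 5 × 5 = 25 | −16.7% |
| 2 | 5 × 4 = 20 | −33.3% |
| 3 | 5 × 3 = 15 | −50.0% |

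For other subscale lengths, one such item costs 1/4 = 25% with 4 items and 1/8 = 12.5% with 8. Two cost 50% and 25%.

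The ordering of infants can also be lost. An infant rated 6 on four applicable items scores 6 × 4 = 24. An infant rated 4 on all six items also scores 4 × 6 = 24. In this case a not-applicable answer counts for less than the lowest rating of 1.

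**Case B: the not-applicable answer is coded 8.** The article speaks of an eight-point scale but gives ratings only from 1 to 7, so this option appears to be the eighth point. The sum is then r(k − m) + 8m. With k = 6 and r = 5:

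- m = 1: 25 + 8 = 33, against 30.
- m = 2: 20 + 16 = 36, against 30.

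The answer now counts for more than the highest rating, and the score is inflated.

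**Case C: mean of the items answered 1 to 7.** The score is r(k − m)/(k − m) = r. With r = 5 it is 5.0 for m = 0, 1, 2 or 3. The prorated sum, k times this mean, is 6 × 5.0 = 30 throughout.

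Both plain-sum codings make the score depend on m, in opposite directions. Averaging or prorating removes that dependence.

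**Does another rule in the article cover this?** Last observation carried forward, in Data analysis, is a general rule for missing data. It does not address an item marked not applicable within a completed questionnaire.

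**The case against.** The strongest objection is that the article condenses a fuller protocol and describes a published questionnaire in a few sentences. The handling of unscored items and a minimum number of answers normally sit in the full document or the scoring syntax, and the word for summation may be shorthand for a prorated score. This stands in part: the absence of a minimum-items rule is not in itself a fault of an article. But the article does more than stay silent. It names the operation, the not-applicable option and the interpretation, and an analyst who follows that text obtains a score that is not comparable.

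Three stronger readings are tempting, and the article supports none of them.

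- **That the affected infants score falsely low.** This requires the option to count as zero. The article gives no code, and coding it as 8 pushes the score up.
- **That the comparison of exposed and unexposed infants is biased.** This requires applicability to differ by exposure, and nothing in the article says that it does. Without such a difference the main effect is noise.
- **That every subscale is affected.** The article does not say which subscales contain items likely to be marked not applicable.

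The size is also conditional. Subscale length is assumed, and the article does not say how often the option would be chosen. A shift in SD units needs a further assumption. With an item-mean SD of 0.8 to 1.2 and ratings of 4 on six items, one unscored item moves the sum by 4/(6 × SD), that is 0.83 to 0.56 SD. This is the displacement of one infant's score. It is not a bias in a group contrast or a regression coefficient, and it should not be set beside the effect of 0.6 used for the sample size.

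Finally, the importance is limited. Infant temperament is exploratory and is not among the primary or key secondary outcomes in the trial registration table.

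**Conclusion.** The point holds as a fault in a stated scoring rule. A plain sum combined with a not-applicable option gives IBQ-R subscale scores that are not comparable between infants or time points.

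If the option adds nothing, the shortfall is m/k: 16.7% for one item and 33.3% for two under the assumption of 6 items per subscale, and 12.5% to 25% for one item with 8 to 4 items. If it is coded as the eighth point, the score is inflated. The direction is undetermined because the code is not given.

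The expected consequence is added noise and possible artefactual change with age. The age effect cannot be sized, since the assessment schedule is in a figure that is not shown and the frequency of the option is unknown. Bias between exposure groups is conditional on applicability differing by exposure. The maternal primary outcomes and the sample size are unaffected.

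**What to change.** Replace the summation sentence with a rule along these lines: each IBQ-R subscale is scored as the mean of its items answered 1 to 7; the not-applicable answer is treated as not scored; a subscale score is computed only if a stated minimum number of its items is answered; and these scores are used in all infant temperament analyses. A prorated sum is equivalent. Half of the items is one possible minimum; the exact threshold is a convention, but it should be fixed before the infant data are analysed.

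The mean treats the answered items as standing for the unanswered ones, so it would help to report the number of not-applicable answers by subscale, time point and exposure group. That would also show whether the conditional concern about exposure groups arises.

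The cost is a few sentences and a change of scoring syntax. No new data are needed.
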